#### Recruitment process

Eligible children will be prospectively recruited through the client database of a state-wide community rehabilitation service. As geographical location and participant availability are critical to forming groups of sufficient participant numbers for this study, participants will be recruited in blocks according to their geographical location. Once at least four, and a maximum of six, children are identified that can attend an eight-week group on a specified day in a specific geographical location, these children will be assigned as group one. When a second group of four to six children are identified for a geographical location, they will be assigned as group two. When two groups of four to six participants each are identified, they will proceed to randomisation.

#### Randomisation

A random sequence will be generated via coin flip by an independent, off-site co-investigator (MA) who will not be involved with assessment or treatment (as per process used in previous studies [17]). The outcome (heads: group 1 = immediate *Sports Stars* intervention, group 2 = waitlist *Sports Stars* intervention. Tails: group 1 = waitlist *Sports Stars* intervention, group 2 = immediate *Sports Stars* intervention) will be written on a piece of paper and concealed inside a sequentially numbered, opaque envelope and stored securely off-site.

When two groups are identified, they will be randomly assigned to either the immediate intervention group or the waitlist control group with a 1:1 block allocation via drawing of one of the opaque envelopes. Randomisation will be completed offsite by the same independent co-investigator (MA). This process will continue until 60 participants complete baseline assessments and proceed to the *Sports Stars* group.

### Therapy protocols and delivery

Refer to Fig. 2 for the study flow diagram according to CONSORT guidelines.

**Fig. 2 Fig2:**
[figure not shown]
Sports Stars flow chart according to CONSORT guidelines

#### Sports Stars intervention

Each group will contain between four and six participants with one lead Physiotherapist. The immediate *Sports Stars* group will receive eight, one-hour, weekly sessions (8 hours) of group-based, sports specific fundamental movement skills training, detailed in Fig. 3. These groups will introduce children to four popular Australian sports and support the development of core motor skills for transition to recreational mainstream and modified sports opportunities including *Junior Entry Point* sports programs, NetSetGo (netball), In2Cricket, MiniRoos (soccer) or T-Ball (softball/baseball). To achieve this, *Sports Stars* will focus on developing key *Body Functions* (aerobic and anaerobic fitness, muscle strength, balance and agility, and locomotor and object control) and sport-specific *Activity* skills to facilitate participation in modified sport games of soccer, netball, T-ball and cricket.

**Fig. 3 Fig3:**
[figure not shown]
Sports Stars session content summary

#### Location

*Sports Stars* will be conducted at local parks in the community in association with Queensland’s largest state-wide community physiotherapy service provider for children with CP. Groups will be provided in urban/regional Queensland, Australia, capturing the breadth of cultural and socioeconomic diversity. Each group will include back-up undercover areas to be used in the event of wet weather.

Participants of the *Sports Stars* group will not be permitted to receive other physiotherapy during their 8 week *Sports Stars* group. Throughout the duration of the study, all participants will be permitted to access standard care from other allied health (e.g. occupational therapy, speech and language pathology) and/or other adjunct therapies. Parents/guardians will be requested to record the frequency, duration and content of any standard care received including any home exercise performed.

#### Standard care comparison

Participants in the *Sports Stars* Waitlist group will receive standard care. This describes the typical intervention that a six to 12-year-old child with a diagnosis of CP would receive from their normal therapists in community, private or hospital contexts. Therapists who provided standard care will have varying degrees of experience working with children with CP. Standard care may include neurodevelopmental therapy, context-focussed therapy, strength or fitness training, or functional training. At this age, children are typically seen for 1:1 therapy, however some group therapy may also be offered. Ambulant children of this age (classified as GMFCS- E&R I-II) with CP would typically receive only 1–2 physiotherapy sessions per quarter. This may include a home program and is expected to vary between participants, however most children would receive no more than two sessions during the comparative 8 weeks of a *Sports Stars* program. Details of frequency, duration and content of any therapy session, particularly physiotherapy, will be collected via a parent log book throughout the project.

### Treatment fidelity

Intervention therapists will be masked to baseline outcome assessments. All intervention therapists providing the *Sports Stars* intervention will be qualified physiotherapists with experience working with children with CP in a community setting. At therapist training, the detailed *Sports Stars* protocol and a sports equipment pack will be provided to all therapists to ensure that participants in all groups received consistent delivery. This includes a written week by week program of sports focussed exercises and progressions (Additional file 1) with detailed instructions and video resources that therapists can use to select predetermined difficulty levels to suit each child’s age, goals and preferences. Therapists will receive individual, face to face training in the *Sports Stars* protocol by the first author prior to the commencement of the group. Treating therapists will engage in further consultation as required with the study coordinator either by phone or in person to review the *Sports Stars* package and to discuss program content and structure prior to providing the group to participants. Each child will have features of their participation in each group session recorded by the treating therapist, including exercise type, level of difficulty and therapist observed engagement. At week three and six of the study, each therapist will undergo fidelity review and receive guidance via email through an independent, offsite co-investigator (MA) who will not be involved with assessment or treatment regarding intervention format, content, progression and data recording. Independent content analysis will determine compliance with the provided protocol. Parents of both the immediate and waitlist groups will be provided with training journals to record any therapy, including home exercises, and sport that they undertake during the study period.

### Outcome measures and procedures

All outcomes will be collected pre-intervention, immediately post intervention and at 12 weeks post intervention by the blinded chief investigator (GC).Classification of Sample

Participants will be classified based on their severity and age to compare groups at baseline. They will be classified according to:**Gross motor function:**
*Gross Motor Functional Classification System (GMFCS-E&R)* [33]

The Gross Motor Function Classification System is an internationally recognized classification system for children and youth with CP. Participants will be classified as either classified as GMFCS- E&R I (able to walk independently at home, school, outdoors and in the community with limitations in speed, balance or coordination) or II (able to walk in most settings, however may have difficulty with distances or more challenging environments and gross motor skills like running and jumping) using the descriptors for between the child’s 6th and 12th birthday [33].b.
**Classification of CP**

Participants will be classified by motor type (spasticity, dyskinesia, ataxia or unclassifiable) and distribution (unilateral or bilateral) [34, 35].c.**Functional mobility:**
*Functional Mobility Scale (FMS)* [36]

Participants will be classified by their ability to walk five, 50 and 500 m, correlating to their ability at home, school and community. Scores range from N (does not apply), to 6 (independent on all surfaces without aids) [36].2.**Outcomes:** Measured for all participants at four time points and compared to baseline and each other:Time one (T1): *zero months*- BaselineTime two (T2): *2 months*- Immediately after immediate interventionTime three (T3): *5 months*- 12 weeks after immediate intervention

For children participating in the waitlist group, an optional fourth assessment will occur:Time four (T4): approximately *8 months*- Immediately after waitlist intervention

### Body function and structure outcomes

#### Aerobic capacity & agility: *10 × 5 Meter Sprint Test* [37]

The 10 × 5 Meter Sprint Test is designed to measure aerobic capacity and agility in children with CP of GMFCS- E&R level I or II. Children must continuously sprint the five-meter course 10 times, making turns at the cones marking the end of the five meters. The 10 × 5 Meter Sprint Test has excellent inter-observer (ICC > 0.97) and test-retest reliability (*r* = 1). It has reported good construct validity. The 10 × 5-m sprint test is sensitive to change for children at GMFCS- E&R levels I and II and therapists report a high clinical feasibility. A decrease in exercise time of 3.2 s would be considered real change [37].

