### Secondary hypotheses

**H2: Body function and structure:** Compared to children in the standard care group, children in the *Sports Stars* group will demonstrate greater improvements in lower limb and upper limb strength, balance, agility and their aerobic and anaerobic fitness.

**H3: Activity:** Compared to children in the standard care group, children in the *Sports Stars* group will demonstrate greater improvements in gross motor capacity, including locomotor ability and object control skills.

**H4: Participation:** Compared to children in the standard care group, children in the *Sports Stars* group will demonstrate increased participation in physical activities including recreational or formal sporting activities.

**H5: Quality of life:** Compared to children in the standard care group, children in the *Sports Stars* group will demonstrate greater improvements in quality of life as measured by parent report.

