#### Anaerobic Capacity *Muscle Power Sprint Test (MPST)* [37]

The MPST measures anaerobic capacity by asking the participant to sprint 15 m (marked by lines and cones) at their maximum pace, 6 times, with 10 s recovery between each sprint. The MPST has a high inter-observer and test-retest reliability (*r* = 0.97–0.99). It has good construct validity with GMFCS- E&R [37] and the Wingate Anaerobic Test (Peak Power: *r* = 0.731, Mean Power: *r* = 0.903) [38]. It is sensitive to change in children GMFCS- E&R level I and II and has high clinical feasibility. Standard errors of measurement were reported at 13.9 (peak power) and 9 (mean power) Watts [37].

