## Analyses

Statistical analysis will be performed using SPSS statistical software. Primary analysis will use the intention to treat principle, using the last observation recorded for participants who withdraw from the program.

Baseline data will be reported using descriptive statistics for each variable (individual sports related activity and participation goals, GM capacity, aerobic fitness, anaerobic fitness and agility, functional strength, participation and quality of life) to establish any difference between randomised groups. The method of aggregation will depend on the normality of the data and will include the mean and standard deviation (normally distributed data) or the median and interquartile range (non-normally distributed data). If characteristics are not comparable at baseline, they will be modelled as covariates in subsequent analyses in order to adjust their possible confounding effects. Linear mixed models will be used to evaluate the effectiveness of the *Sports Stars* intervention compared to the waitlist control on the primary outcome (COPM). Linear mixed models take into account variation in individuals over time, are able to manage missing data without excluding participants for further analysis and examine changes in the outcomes over time as well as across the two groups. Significance will be set at *p* < 0.05. Residuals of the fitted models will be examined to ensure that all required assumptions are met.

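### H2 predicts a gain in aerobic fitness, but the only outcome labelled aerobic is a timed 50 m shuttle sprint with no aerobic criterion named, so a faster time should not be reported as better aerobic fitness

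*Protocol article*

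**What the plan says.** Under Secondary hypotheses, H2 expects greater improvement with Sports Stars in "lower limb and upper limb strength, balance, agility and their aerobic and anaerobic fitness". Agility, aerobic fitness and anaerobic fitness are thus three separate components. The section Sports Stars intervention also lists aerobic fitness among the body functions that the programme sets out to develop.

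Under Body function and structure outcomes, the first test is headed as a measure of aerobic capacity and agility. The text says that the 10 × 5 "Meter Sprint Test is designed to measure aerobic capacity and agility in children with CP" and describes the task: "Children must continuously sprint the five-meter course 10 times, making turns at the cones marking the end of the five meters". The score is a time: "A decrease in exercise time of 3.2 s would be considered real change". On validity, the text offers "It has reported good construct validity" and names no comparator.

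The next test, the Muscle Power Sprint Test (MPST), is headed as anaerobic capacity. Children "sprint 15 m (marked by lines and cones) at their maximum pace, 6 times, with 10 s recovery between each sprint". It cites the same source [37] and reports correlations with the Wingate Anaerobic Test of 0.731 (peak power) and 0.903 (mean power).

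The Analyses section, in its sentence on describing baseline data, lists "GM capacity, aerobic fitness, anaerobic fitness and agility, functional strength" among the variables.

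**The concern.** A hypothesis about a construct needs an outcome that can be read as that construct. Here the aerobic component of H2 depends on one short, timed sprint with turns. If the labels are followed, a child who completes the shuttle faster will be reported as having gained aerobic fitness. Better turning or acceleration could produce the same faster time, and agility is something the programme trains directly. The single time carries both labels, so it cannot show which of the two changed. A positive result could then enter the literature as evidence that an eight-session sports group improves aerobic fitness, when what was observed was a quicker 50 m shuttle.

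**Working it through.** This is a question of what is measured, so no power or sample-size formula applies. The check has four steps.

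**1. Map each component of H2 to an outcome, using the outcome sections.**

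| H2 component | Outcome so labelled or described |
|---|---|
| Lower limb strength | Standing broad jump, vertical jump |
| Upper limb strength | Seated throw |
| Balance | Timed up and go |
| Agility | 10 × 5 m sprint |
| Aerobic fitness | 10 × 5 m sprint (same score) |
| Anaerobic fitness | MPST |

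One score serves two components, and aerobic fitness has no other outcome.

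**2. Look for sustained effort elsewhere.** The remaining measures are COPM, GMFM Challenge, TGMD-2, CAPE/PAC, CP QOL-Child, and the satisfaction and engagement scales. These are goal ratings, observed motor skill and questionnaires. As described, none records an endurance distance, a graded exercise stage, heart rate or oxygen uptake. Count of sustained-effort measures: 0.

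**3. Set the two sprint tests side by side.**

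| | 10 × 5 m test | MPST |
|---|---|---|
| Label | Aerobic capacity and agility | Anaerobic capacity |
| Structure | Continuous, with turns | Intermittent, 10 s recoveries |
| Distance | 10 × 5 = 50 m | 6 × 15 = 90 m |
| Recovery | None | 5 × 10 = 50 s |
| Cited source | [37] | [37] for the test; an anaerobic comparison is also cited |
| Criterion named | None | Wingate Anaerobic Test, r = 0.731 and 0.903 |

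The article gives no completion time for the 10 × 5 m test. Assuming a mean speed v, turns included, of 1.0 to 3.0 m/s, duration = 50 / v:

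- v = 1.0 m/s: 50 / 1.0 = 50 s
- v = 2.0 m/s: 50 / 2.0 = 25 s
- v = 3.0 m/s: 50 / 3.0 = about 17 s

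Across the assumed range the task lasts under a minute.

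**4. Compare the labels within the document.** The test's own heading pairs agility with aerobic capacity. The baseline list reads "GM capacity, aerobic fitness, anaerobic fitness and agility, functional strength", which pairs agility with anaerobic fitness and lists aerobic fitness separately. If agility sits with the anaerobic tests, the list leaves aerobic fitness with no test of its own. If it sits with the aerobic test, the list contradicts the outcome section.

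**The case against.** The strongest reply is that the protocol says what the test measures, reports construct validity and cites a source. That source is not available here, and the document nowhere says that the test fails to measure aerobic capacity. This stands in part. The view that a sub-minute sprint is a poor index of aerobic fitness rests on the task as described and on general physiology, and the duration comes from assumed speeds. A reader might therefore infer that the test has been shown to be invalid, or that the trial could never support any aerobic conclusion. The documents do not carry that. They show that no aerobic criterion is named and that the labels disagree.

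Three other stronger readings also fail:

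- **Shorter, so not aerobic.** A reader might take 50 m against 90 m as proof. Total distance does not settle which energy system is used, and one test is continuous while the other is intermittent.
- **An all-out test.** The 10 × 5 m text speaks of continuous sprinting; an instruction to go at maximum pace appears only for the MPST.
- **A planned effect analysis of aerobic fitness.** The list in Analyses describes baseline data. The mixed model in that section is specified for COPM. The list supports the point about inconsistent labels and nothing more.

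The aerobic label may be a slip for anaerobic. The document does not settle this. If it is a slip, H2 and the baseline list would still name aerobic fitness with no outcome behind it.

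Nor is this a matter of article-length condensation: the hypothesis, the task and the construct are all stated, and they do not fit together.

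**Conclusion.** The concern holds in this form: the only outcome labelled aerobic is a timed 50 m shuttle sprint, shared with agility, with no aerobic criterion named and with labels that differ between sections. On what the article shows, a faster time should be reported as better agility or short-sprint performance, and not as improved aerobic fitness.

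Its size is one of the six body-function components of H2. The primary COPM hypothesis, the sample size, the randomisation and the other components of H2 are unaffected, and the sprint time itself remains a usable result under a suitable label. The conclusion assumes that the test is run as the article describes it and that no sustained-effort measure exists beyond those listed. It would soften if the cited source supplied an aerobic criterion for this test, although one score would still be serving two constructs.

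**What to change.** 1. In Body function and structure outcomes, relabel the 10 × 5 m test as agility/short-sprint performance.
2. Remove the word aerobic from H2, and remove aerobic fitness from the baseline variable list in Analyses, so that agility is grouped consistently in both places.
3. In Sports Stars intervention, where aerobic fitness is a programme target, or alongside the outcomes, state that it is not assessed in this trial.
4. Record the change as a dated amendment to a secondary hypothesis, since the trial is registered and H2 is pre-specified.

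Cost: no new test, no added assessment time and no change to the sample size. The downside is that one fewer construct can be claimed and a stated programme target goes unmeasured. Adding an endurance measure would keep the aerobic component, but it would lengthen the two-hour assessments and would help only children not yet assessed at baseline; the relabelling does not depend on it.

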#### Anaerobic Capacity *Muscle Power Sprint Test (MPST)* [37]

The MPST measures anaerobic capacity by asking the participant to sprint 15 m (marked by lines and cones) at their maximum pace, 6 times, with 10 s recovery between each sprint. The MPST has a high inter-observer and test-retest reliability (*r* = 0.97–0.99). It has good construct validity with GMFCS- E&R [37] and the Wingate Anaerobic Test (Peak Power: *r* = 0.731, Mean Power: *r* = 0.903) [38]. It is sensitive to change in children GMFCS- E&R level I and II and has high clinical feasibility. Standard errors of measurement were reported at 13.9 (peak power) and 9 (mean power) Watts [37].

#### Functional Lower Limb Strength: *Standing Broad Jump* [39]

The standing broad jump measures lower limb strength in the context of sports participation. Standing with toes up to a line, children are asked to jump forward as far as they can, landing with both feet. The distance between the start line and the most distal part of their toes of their back foot will be measured for three jumps, with the average recorded to the nearest centimetre. The standing broad jump has excellent test-retest reliability in typically developing children (ICC- 0.88 [40]) and in children with down syndrome (ICC- 0.89 [41]). It has excellent concurrent validity with measures of physical fitness (*r* = 0.84) [40], Paralympic throwing (*r* = 0.77–0.86) [42] and sprinting (*r* = 0.82) [43] for children with disabilities. It has been reported to be sensitive to change as part of a test battery and is a feasible clinical test [40].

#### Functional Lower Limb Strength: *Vertical Jump* [39]

The vertical jump measures lower limb strength. Standing next to a wall, children raise their arm. The most distal point of their fingers is marked. They are instructed to jump as high as they can, a second mark being made at the height of their jump. The vertical distance of three jumps will be measured and averaged to obtain the jump height to the nearest centimetre. The vertical jump has been used to represent the core functional output of children’s strength in previous literature [44]. It is also utilised readily in mainstream sport and physical education and is included in Australia’s national talent identification and development program [39].

#### Functional Upper Limb Strength*: Seated throw* [39]

The seated throw measures functional upper limb strength. Children are seated comfortably with their back against a wall. Using a chest pass, they are asked to throw a basketball as far as possible while keeping their back against the wall. The distance between the wall and the first point of contact of the ball will be measured to the nearest centimetre for three throws and the average calculated. Similar to the vertical jump, the seated throw has been used to represent the core functional output of children’s strength in previous literature [44, 45], is common and clinically feasible in mainstream sport and physical education and is included in Australia’s national talent identification and development program [39].

